### Data collection supervision and training

SEACO is an ISO-certified research platform for its operations, therefore training and supervision are carried out in accordance with SEACO’s standard operating procedures. All data collectors are required to be fluent in the local language (Bahasa Melayu or Malay language or Mandarin) and have at least a working knowledge of English. To ensure data quality and consistency across interviewers, the field supervisor will undertake random concurrent supervisory visits to observe practice. The data collectors will also be periodically observed by the project leader and the field manager. Based on the scoring completed during these observation sessions, onsite training or re-training will be carried out as appropriate. Data collection is undertaken on Samsung Galaxy tablets. The data are encrypted on the tablet to ensure they are secure and inaccessible in the unlikely event that they are mislaid by data collectors. Transfer of data from the tablet to the remote server is done on a weekly basis. The data are also encrypted on the server and backed up by servers at Monash Sunway Campus and at Monash Clayton. Research staff have limited access to anonymised data.

### Data monitoring

All expected and unexpected adverse events reported by participants will be recorded in an events register and reported to the Human Research Ethics Committee. Due to the nature of the treatment products, that is, commercially available food products, no adverse events are expected. However, if participants feel in anyway adversely affected by any foods or the principal investigator feels an adverse event necessitates cessation, the participant would be advised not to continue and the appropriate measures will be taken (ie, record in field notes, contact research nurse and principal investigator if deemed necessary).

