### Purpose and aims

The overall objective of the DePEC-Nutrition feasibility study is to demonstrate the acceptability of a dietary intervention to increase the consumption in high-nitrate green leafy vegetables and reduce salt intake over a 6-month period among Malaysian adults with raised blood pressure. The objectives focus on the core areas of a trial that need to work for the study to succeed procedurally, such as recruitment ability and participant retention, data collection procedures and assessment methods used, potential to deliver the dietary intervention and resource requirement. Information on the effect size of the intervention on cognition and blood pressure will also be determined, which will be instrumental in the design and calculation of the sample size of a follow-on efficacy trial.

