**Figure 1 F1:**
[figure not shown]
A flow diagram providing an overview of the study procedures.

An interim 2-month visit will take place for those in the intervention groups only, to provide reinforcement messages relating to the allocated dietary intervention and with a view to enhancing compliance with the intervention. In addition, a brief adherence questionnaire will be administered, body weight and resting blood pressure will be measured and salivary strip and spot urine samples will be collected. The same measurements and further dietary reinforcement messages will be conducted at an interim 4-month visit for the participants allocated to the intervention arms. Participants in the control arm will only have one interim visit at month 4 and will have their weight and blood pressure measured. The end of study visit (at KK, Segamat) will include the conduction of the measurements collected at baseline, including cognitive assessment, dietary assessment and collection of biological samples (blood, dried blood spots, 24-hour urine and spot urine samples, saliva samples, salivary strips). In addition, an exit group session (focus group evaluation) and a self-administered feedback questionnaire will be scheduled to evaluate the adherence to the interventions and obtain detailed feedback on the overall study protocol. Finally, the participants will be offered a token of appreciation to acknowledge their participation in the study and to compensate for travel expenses. This is usually to the value of RM 25.

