### Outcome measures

Outcome assessments will be conducted at baseline, month 4 and month 6 for all groups, with an additional assessment visit at month 2 for those in the intervention groups. Assessments at baseline and month 6 will be conducted in clinic/at home, with remaining assessments completed in the participants own home. The same instruments will be used for measurements at each time point. Assessors are trained prior to the assessments to follow a standardised protocol. A timeline of the study procedures can be found in table 1.

**Table 1 T1:** Timeline of study procedures

Procedures	Consent/screening	Baseline Week 1	Week 2	Week 4	Week 6	Week 8	Week 10	Week 12	Week 16	Week 18	Week 20	Week 22	End of study Week 24
Inclusion/exclusion	✓												
Consent	✓												
Activities for intervention group													
Dietary education		✓											
Reinforcement at home visit		✓				✓			✓				
Group education counselling session		✓											
Home visit						✓			✓				
SMS messages			✓	✓	✓	✓	✓	✓	✓	✓	✓	✓	✓
Activities for control group													
General health promotion message		✓											
Home visit									✓				
Study measurements													
Sociodemographic		✓											
Concomitant medication check list		✓				✓							✓
Any medical events		✓				✓							✓
Physical activity (IPAQ)		✓											✓
Depression (GDS)		✓											✓
Food Frequency Questionnaire (FFQ)		✓											✓
24-hour dietary recall		✓											✓
Nitrate: urine		✓*				✓†‡			✓‡				✓*
Salt: urine		✓*				✓†‡			✓‡				✓*
Cognitive performance		✓											✓
Resting blood pressure		✓				✓†			✓				✓
Body composition		✓				✓†§			✓§				✓
Physical function		✓											✓
Blood sample and dried blood spot		✓											✓
Saliva sample and salivary strips		✓	✓†¶	✓¶	✓

*Twenty-four hour urine and spot urine samples.

†Intervention groups only.

‡Spot urine sample only.

§Body weight only.

¶Saliva strips only.

FFQ, Food Frequency Questionnaire; GDS, Geriatric Depression Scale; IPAQ, International Physical Activity Questionnaire.

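### Table 1 schedules medical-event and medication checks once after baseline for controls, twice for the intervention arms, and never at week 16, the one interim visit shared by all arms

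*Protocol article*

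**What the plan says.** Three parts of the protocol article bear on this point.

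- **Data monitoring.** "All expected and unexpected adverse events reported by participants will be recorded in an events register", and these are passed to the ethics committee.
- **Outcome measures, Table 1.** The rows "Any medical events" and "Concomitant medication check list" are each ticked at baseline (week 1), week 8 and week 24, with no footnote mark. Their week 16 cells are empty. Other week 8 measurement ticks carry the dagger, which means "Intervention groups only". The home-visit row for controls is ticked at week 16 only; the one for the intervention groups is ticked at weeks 8 and 16.
- **Study procedure and Outcome measures, text.** "An interim 2-month visit will take place for those in the intervention groups only". For controls: "Participants in the control arm will only have one interim visit at month 4 and will have their weight and blood pressure measured". The Outcome measures text agrees: "Outcome assessments will be conducted at baseline, month 4 and month 6 for all groups", with the month 2 visit added for the intervention groups.

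**The concern.** The schedule of medical-event and medication checks does not fit the visit plan. Read with the visits that each arm actually has, it asks intervention participants twice after baseline and controls once. It also passes over the only interim visit that all four arms share. The longest stretch without a scheduled question is therefore longer in controls, and events or medication changes between baseline and month 6 are picked up late in every arm.

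Two things are at stake. The first is ordinary safety follow-up in people with raised blood pressure, some of them on treatment. The second is evenness: if anyone later sets out events by arm, the arms will have been asked at different intervals. The Purpose and aims section lists "data collection procedures and assessment methods used" among the things that this feasibility trial examines, so this is a good stage at which to correct the schedule.

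**Working it through.** The plan gives no figure to reproduce. The check reads Table 1 by column and sets it against each arm's visits.

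**Step 1: the ticks.** Both rows are intact in the extracted text, and each tick falls under baseline week 1, week 8 and week 24. As an alignment check, the blood pressure row read in the same way gives baseline, week 8 (dagger), week 16 and week 24, which agrees with the text on visits.

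**Step 2: the visits.** Intervention arms: weeks 1, 8, 16 and 24. Control arm: weeks 1, 16 and 24.

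**Step 3: checks that can take place after baseline, per person.**

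| | Checks | Gaps between checks (weeks) |
|---|---|---|
| Intervention arms | 2 (weeks 8, 24) | 8 − 1 = 7; 24 − 8 = 16 |
| Control arm | 1 (week 24) | 24 − 1 = 23 |
| Any arm at week 16 | 0 | – |

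**Step 4: the footnote marks.** Six study-measurement rows are ticked at week 8, leaving aside the saliva row, whose layout is broken in extraction.

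- With the dagger (4): urine nitrate, urine salt, blood pressure, body composition.
- Without it (2): medical events, concomitant medication.

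Taken literally, the table schedules these two checks for controls at a visit that controls do not have.

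**Step 5: the effect of adding week 16 for all arms.** Control gaps become 16 − 1 = 15 and 24 − 16 = 8 weeks. Intervention gaps become 7, 16 − 8 = 8 and 8 weeks. The longest gap falls from 23 to 15 weeks in controls and from 16 to 8 in the intervention arms. A difference in prompting remains unless events by arm are described over windows common to all arms: baseline to week 16 (15 weeks) and week 16 to week 24 (8 weeks).

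**The case against.** **No planned comparison is harmed.** Adverse events are not in the feasibility table, the secondary outcomes or the statistical analysis section. Data monitoring deals with handling single cases and expects no adverse events. This stands, and it keeps the point minor.

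**The link to the register is inferred.** Nothing says that the medical-events row feeds the events register; it could simply update the medical history. This also stands. The row is nevertheless the only scheduled event item in Table 1, and the uneven schedule is there whichever purpose it serves.

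**The missing dagger is editorial.** The text and the control home-visit row already settle that week 8 is for the intervention arms. That is so, but settling it this way is what leaves controls with a single check.

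**Other routes exist.** Participants may report at any time, week 24 can pick up earlier events, and the exit questionnaire and focus groups invite feedback, the latter including side effects. This is fair: the difference lies in prompting and look-back, not in whether an event can be recorded. The focus groups cover a purposive subset after the intervention and are not tied to the register.

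**Month 4 might already include the check.** The text repeats the month 2 measurements at month 4 for the intervention arms. Its month 2 list does not mention medical events, however, and Table 1 leaves week 16 blank.

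**Stronger readings that the document does not support.**

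- A reader might infer from Data monitoring that events found by staff or at measurements are shut out of the register. The sentence does not say so, and how such findings are entered is detail that a condensed article leaves to the full protocol and procedures.
- A reader might also turn the gaps into a bias. Suppose that events more than 8 weeks old are reported r times as often as newer ones and that true rates are equal and constant. The ratio of recorded events, intervention to control, is then (7 + 8 + 8r)/(8 + 15r): 1.00 at r = 1, 21/19.25 = 1.09 at r = 0.75, and 19/15.5 = 1.23 at r = 0.5. Neither the 8-week cut-off nor r comes from the document, so this is illustration only.

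**Conclusion.** The point holds as a minor matter of safety ascertainment. Per person, the plan fixes one scheduled check after baseline in controls against two in the intervention arms, longest gaps of 23 against 16 weeks, and none at the shared week 16 visit. Two week 8 ticks lack the footnote mark that the visit plan requires.

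This rests on the column reading of Table 1 and on the text that gives controls no month 2 visit. That the medical-events row prompts register entries is an inference. The size of any resulting difference in reporting cannot be derived from the document, which gives neither an event rate nor a recall rate. The sample size and the planned analyses are not affected.

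**What to change.** 1. In Table 1, tick both the medical-events and the concomitant-medication rows at week 16 for all arms.
2. Put the intervention-groups-only dagger on both week 8 ticks.
3. If event counts are ever described by arm, base them on windows common to all arms: ask at week 16 about the time since baseline, and at week 24 about the time since week 16. Keep week 8 reports, but list them separately.

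This reduces the difference in prompting but may not remove it: intervention participants will still have been asked at week 8 and have more contact with the study. The cost is two ticks, two footnote marks and a few minutes at a visit already scheduled. The other drawback is that intervention participants may repeat at week 16 what they said at week 8, and those week 8 reports stay out of any description by arm. No new visit or measurement is needed.

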## Discussion

This study will demonstrate the feasibility of a dietary intervention to increase the consumption of high-nitrate green leafy vegetables and reduce salt intake over a 6-month period among Malaysian adults with raised blood pressure. The design of this feasibility study has taken into account the evidence collected in developed countries on the efficacy of complex interventions for the prevention of cognitive decline and evidence on the major transitions in dietary patterns occurring in developing countries as a result of nutrition transition trends. An increased consumption of vegetables and reduction of salt intake are key dietary recommendations for the prevention of cardiometabolic diseases. Our hypotheses are that a targeted, educational approach, to encourage healthy dietary choices focused on these key elements of the diet, would be linked to greater long-term adherence to the interventions and improved cognitive function with prospective, projected reduced risk of dementia in these populations. This mixed-method feasibility study will provide key quantitative and qualitative information on the delivery of a novel dietary intervention and will aim to estimate the effect size of the single and combined interventions on cognitive function and blood pressure, which will be instrumental in the design and calculation of the sample size of a larger, follow-on efficacy trial.
